### Statistical considerations

#### Sample size calculation

Based on available retrospective data, median HPFS following BE is estimated at 11 months and cTACE at 20 months [9], corresponding to an HR of approximately 1.8. The effect of cTACE and DEB-TACE is presumed to be equivalent. Assuming a two-sided type I error rate of 10%, 60 participants per arm will provide at least 92% power for the overall log-rank test and 87% power for pairwise tests.

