**Methods/design:**

A prospective, open-label, multicenter randomized controlled trial will be conducted in patients with progressive or symptomatic unresectable NET liver metastases. Patients will be randomized to treatment with bland embolization, lipiodol chemoembolization, or drug-eluting microsphere chemoembolization, with 60 enrollees per arm. The primary endpoint will be hepatic progression-free survival (HPFS) following initial embolotherapy by RECIST criteria. The sample size is powered to detect an HR of 1.78 for HPFS following chemoembolization compared with bland embolization, which was estimated on the basis of existing retrospective studies. Secondary endpoints include overall progression-free survival, duration of symptom control, quality of life, rate of adverse events, and interval between embolotherapy cycles. Interim safety analyses will be performed at 10 and 30 patients per arm.

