### Statistical analysis

Our analysis will be aimed at identifying any embolotherapy arm that is significantly inferior (or superior) to the others based on comparison of the primary outcome. Our null hypothesis assumes that the arms are equivalent, without preconceived ranking. The test will use a studentized range approach developed for phase II screening trials using survival data [26, 27]. We will estimate the survival hazard rate in each treatment arm and compute the range of log-hazard rates (largest minus smallest). We will then compare the observed range to the distribution of the range under the null hypothesis. If the observed range exceeds the 95th percentile of its null distribution, any group whose hazard rate differs by more than this critical value from the group with the lowest PFS hazard will be declared significantly worse.

For secondary outcomes including symptom relief interval, time to reembolization, overall PFS, and PFS for subsets of the study sample, we will estimate the survival distribution using the Kaplan-Meier method. Comparisons among groups will be performed using log-rank tests, and survival regression models will be developed to estimate treatment effects, adjusted for baseline variables that may affect treatment outcomes.

For continuous outcomes (e.g., quality of life and symptom scores), summary statistics (mean, SD, 95% CI) will be assessed for each of the study arms, and comparisons among arms will be performed using one-way analysis of variance and *t* tests. Regression models will be used to estimate treatment effects adjusted for baseline variables that may affect treatment outcome. Binary variables (e.g., biomarkers) will be tabulated by treatment arm and compared using the chi-square test. Logistic regression models will be used to estimate adjusted effects.

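### The stated 92% and 87% power belong to log-rank tests at 10%; the planned primary test, a studentized range at the 95th percentile, has about 82–86% and 68–71% with 60 per arm

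*Protocol article*

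**What the plan says.** In the protocol article, the Sample size calculation section sets the error rate and the overall power in one sentence, "Assuming a two-sided type I error rate of 10%, 60 participants per arm will provide at least 92% power for the overall log-rank test", and continues with "87% power for pairwise tests". The effect comes from retrospective data: "median HPFS following BE is estimated at 11 months and cTACE at 20 months [9], corresponding to an HR of approximately 1.8". The abstract gives the design HR as 1.78. The configuration is BE worse than two equal TACE arms: "The effect of cTACE and DEB-TACE is presumed to be equivalent".

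The Statistical analysis section describes the primary test. A hazard rate is estimated in each arm, and the range of the three log-hazard rates (largest minus smallest) is compared with its null distribution. The decision rule begins "If the observed range exceeds the 95th percentile of its null distribution"; any arm that exceeds the lowest-hazard arm by more than the critical value is then declared worse. The same section assigns log-rank tests to the secondary time-to-event outcomes. No power is given for the range test.

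**The concern.** The power statement and the primary analysis differ in two respects: the test (log-rank, overall and pairwise, against a three-group studentized range) and the error rate (10% against 5%). Reading a two-sided 10% as a one-sided 5% does not help. A range has no direction, so exceeding its 95th percentile under the null is a 5% error over all three arms, and the protocol says it has no preconceived ranking.

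Two things are at stake. First, the 60 per arm are justified by power that the planned analysis does not have. Second, a result between the 90th and 95th percentiles of the null range would be positive at the error rate in one section and negative under the rule in the other. In an open-label trial, that choice should not be left open until the results are known.

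**Working it through.** **Inputs from the protocol article.** 60 per arm, 1:1:1 (Sample size calculation; Randomization). BE median 11 months. TACE median 20 months (HR 20/11 = 1.818), or HR 1.78, which gives 11 × 1.78 = 19.58 months. Both TACE arms equal. Accrual 24 months, minimum follow-up 24 months (Trial time scale).

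**Assumptions.** Exponential survival, uniform accrual, analysis 24 months after the last enrolment, no dropout.

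**Step 1: events.** With hazard λ = ln 2 / median, accrual A = 24 and follow-up F = 24,

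P(event) = 1 − [exp(−λF) − exp(−λ(F + A))] / (λA).

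- Median 11: 0.886, × 60 = 53.2 events.
- Median 19.58: 0.712, × 60 = 42.7 events.
- Median 20: 0.705, × 60 = 42.3 events.

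**Step 2: reproduce the stated power (log-rank, 10%).**

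One BE–TACE pair at HR 1.78: SE = √(1/53.2 + 1/42.7) = 0.2055, and ln(1.78)/SE = 0.5766/0.2055 = 2.81. Power = Φ(2.81 − 1.645) = 87.7%. With medians 11 and 20 the standardised effect is 2.90 and power is 89.6%.

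Overall test on 2 df at HR 1.78: the event-weighted mean log hazard ratio is 53.2 × 0.5766 / 138.6 = 0.2213. The noncentrality is 53.2 × (0.5766 − 0.2213)² + 85.4 × 0.2213² = 10.9. Against the 10% critical value of 4.605, power is 91.1% (92.8% with medians 11 and 20).

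These match the stated 92% and 87% closely, so the stated figures are log-rank figures at 10%.

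**Step 3: the planned test.** The 95th percentile of the studentized range for three groups with large degrees of freedom is q = 3.314, and q/√2 = 2.344. For one given BE–TACE pair, power = Φ(2.81 − 2.344) = 67.8% at HR 1.78, and 71.1% with medians 11 and 20. Power for any difference was simulated with 400,000 draws of normal log-hazard estimates with variance 1/events. Depending on how unequal event counts enter the variance, it is 82.3–83.5% at HR 1.78 and about 85–86% with medians 11 and 20.

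**Step 4: separate the two causes.** At the 90th percentile q = 2.902 and q/√2 = 2.052.

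| Test | Any difference | One given BE–TACE pair |
|---|---|---|
| Stated in the protocol | at least 92% | 87% |
| Log-rank, 10% | 91–93% | 88–90% |
| Log-rank, 5% | 85–87% | 80–83% |
| Range, 90th percentile | 90–92% | 77–80% |
| Range, 95th percentile (planned) | 82–86% | 68–71% |

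The overall loss comes mostly from 10% against 5%. The pairwise loss comes from both the error rate and the larger critical value of the range.

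**Step 5: what the thresholds mean.** With SE 0.2055, the observed HR needed for one pair is exp(1.645 × 0.2055) = 1.40 for the 10% pairwise log-rank test, exp(2.052 × 0.2055) = 1.52 for the range at the 90th percentile, and exp(2.344 × 0.2055) = 1.62 at the 95th.

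**Step 6: sensitivity of the planned test (any difference / one pair).**

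- 8% of the 60 lost: 79–82% / 63–67%.
- Every patient censored at 24 months: 75–78% / 58–62%.
- Every patient followed to an event: 91–93% / 79–82%.

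Only the last case brings the overall figure near 92%. The stated follow-up does not deliver it, and the pairwise figure still falls short of 87%.

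**The case against.** The strongest reply concerns the pairwise figure. The decision rule does not test BE against a TACE arm named in advance; it compares each arm with whichever arm has the lowest hazard. Under that rule BE is declared worse in about 82–86% of trials at the design effect, so it would be wrong to say that the trial has only two chances in three of its main conclusion. This stands, and 68–71% should be read only as the counterpart of the protocol's own pairwise 87%. It does not rescue that 87%, because the planned rule contains no separate pairwise test to which the figure could apply.

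A second reply is that the choice of test matters little overall, since log-rank at 5% gives 85–87%. That is correct, and it places most of the overall shortfall in the unreconciled error rate.

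A third is that 24 months is a minimum and no analysis date is fixed. With 36 or 48 months' minimum follow-up, the range test's overall power rises to about 86–89% or 88–91%. Even at 48 months it stays below 92%, with a given pair at about 76–79%, and dropout works in the other direction. The exact percentages therefore depend on the assumptions, but the direction of the discrepancy does not.

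**Conclusion.** The power statement is wrong as written. The 92% and 87% describe log-rank tests at a two-sided 10%, which the protocol does not plan for its primary outcome. The planned range test at the 95th percentile has about 82–86% power for any difference, 6 to 10 points less, and about 68–71% for BE against one given TACE arm, 16 to 19 points less. The overall chance of missing the design effect rises from the stated 8% at most to about 14–18%.

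These figures assume exponential survival, uniform 24-month accrual, 24 months' minimum follow-up and no dropout, with the design HR between 1.78 and 1.82. The conflict in test and error rate needs no assumption: it is in the text. Because it concerns the error rate and power of the primary analysis, it must be corrected.

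**What to change.** State one primary test and one overall type I error rate in both sections, and quote power for that test with its assumptions on event times, accrual, follow-up and dropout.

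- If the 95th percentile stays, the Sample size calculation section should give a 5% overall error for the studentized range test, with power at HR 1.78 of about 82% for any difference and about 68% for BE against one given TACE arm. It should add that, under the planned comparison with the lowest-hazard arm, BE is declared worse with about 82% probability.
- If 10% was intended, the Statistical analysis section should use the 90th percentile, and power at HR 1.78 is about 90% and 78%.

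The first option leaves the primary decision rule untouched and costs only a less favourable power statement. The second relaxes the rejection rule in a trial that began enrolling in March 2017, so it should be a dated amendment made before any comparison of outcomes between arms. Neither needs extra patients. If power near 92% is still wanted at 5%, it would have to come from more events, and that should be decided openly.

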### Randomization

The study will enroll 180 patients, who will be randomized in a 1:1:1 ratio to the three treatment arms. Randomization will be performed centrally and stratified by institution, using blocks of randomly selected sizes (3, 6, or 9). Patients with symptomatic but not progressive liver disease will be monitored during the accrual phase to ensure balanced allocation between treatment arms, with adjustment as necessary.

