### Study design

This is an open-label, multicenter, randomized trial comparing three embolotherapy techniques for NET liver metastases: (1) BE, (2) cTACE, and (3) DEB-TACE. The study flowchart is shown in Fig. 1. Anticipated study sites include academic hospitals in the United States, Australia, Canada, France, and Argentina.

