• Participants aged 18 years and older • Biopsy-proven neuroendocrine tumor with tumor burden dominant in the liver • Measurable metastasis to liver with at least one dimension ≥1.0 cm. Known extrahepatic disease should be limited to lymph nodes of < 2 cm and/or any bone metastases. • Liver tumor burden ≤ 70% of the total liver volume by visual estimate • Not a candidate for surgical resection owing to unresectability, anatomy, anesthesia risk, patient preference • Symptoms uncontrolled by somatostatin analogues OR morphologically progressive tumor by RECIST 1.1 criteria in the liver OR baseline tumor burden > 25% of the liver volume • No plans for the patient to receive other concomitant therapy while on this protocol treatment (other than octreotide or bisphosphonate therapy) • Performance status 0–2 on Zubrod performance scale • Serum creatinine ≤ 2.0 mg/dl • Serum bilirubin ≤2.0 mg/dl • Serum albumin ≥3.0 g/dl • Platelet count ≥ 50,000/μl (corrected if needed) • INR ≤ 1.5 (corrected if needed) • All patients must be informed of the investigational nature of this study and must sign a study-specific informed consent form in accordance with institutional and federal guidelines prior to study entry.	• Pregnant or lactating women may not participate, owing to the embryotoxic effects of protocol treatment. • Women/men of reproductive potential may not participate unless they have agreed to use an effective contraceptive method. • Prior hepatic arterial therapy or hepatic radiation therapy. Prior surgical resection or ablation of liver metastases is acceptable. Patients must be at least 1 month beyond prior chemotherapy, PRRT, ablation, or surgery and must have recovered from all therapy-associated toxicities. • Active infection (symptomatic bacterial and fungal infection, newly diagnosed and/or requiring treatment) • Choledochoenteric anastomosis, transpapillary biliary stent, or sphincterotomy of duodenal papilla • Absolute contraindication to intravenous iodinated contrast agent (history of significant previous contrast agent reaction not mitigated by appropriate premedication) • Allergy to doxorubicin • Contraindications to arteriography and selective visceral catheterization: ○ Severe allergy or intolerance to contrast media, narcotics, sedatives, or atropine * ○* Bleeding diathesis not correctable by usual forms of therapy * ○* Severe peripheral vascular disease precluding catheterization • Contraindications to hepatic artery embolization: * ○* Portal vein occlusion without hepatopedal collateral flow demonstrated by angiography or portal hypertension with hepatofugal flow * ○* Hepatic encephalopathy

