### Investigations and interventions

#### Baseline evaluation

Clinical assessment, patient-reported NET quality of life (European Organization for Research and Treatment of Cancer [EORTC] QLQ-C30 and G.I.NET21 questionnaires) and Carcinoid Symptom Severity Score [24], screening laboratory studies (complete blood count, partial thromboplastin time, internal normalized ratio, comprehensive metabolic profile, tumor markers including chromogranin A), and imaging (abdominal computed tomography [CT] or magnetic resonance imaging [MRI], chest CT) will be performed within 30 days of initial embolotherapy. Patients with tumors without available histologic grading (WHO 2010) must undergo percutaneous biopsy to determine tumor grade. Once the eligibility data forms are completed in the ORACLE database (Oracle, Santa Clara, CA, USA) and baseline images are uploaded to the Imaging Core and undergo a quality control check, the treatment assignment is automatically generated via a built in block randomization program (*see* “Randomization” section below).

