### Study objectives

#### Primary endpoint

The primary endpoint is HPFS from initial embolotherapy by Response Evaluation Criteria in Solid Tumors (RECIST) 1.0 criteria, as determined by blinded central review of follow-up imaging. Because all of the embolization techniques are in common clinical use, there will be no formal interim efficacy analysis.

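### Open-ended adjustment of allocation for symptomatic, non-progressive patients is an avoidable risk of bias that gains little; leave the random sequence alone and account for entry status in the HPFS analysis

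*Protocol article*

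**What the plan says.** The protocol article (Randomization) states that 180 patients "will be randomized in a 1:1:1 ratio to the three treatment arms". Randomization is central, institution is the only stratification factor, and block lengths of 3, 6 or 9 are chosen at random. Under Baseline evaluation, once the eligibility forms are complete and the baseline images have passed quality control, "the treatment assignment is automatically generated via a built in block randomization program".

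The Randomization section then singles out one group, those whose liver disease causes symptoms but is not progressing. These patients "will be monitored during the accrual phase to ensure balanced allocation between treatment arms, with adjustment as necessary". The article gives no reason for choosing this group, no degree of imbalance that would trigger action, no method of adjustment, and no party responsible for it.

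Three other statements bear on the point:

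- **Blinding.** Treatment is not blinded (Study design): "This is an open-label, multicenter, randomized trial comparing three embolotherapy techniques for NET liver metastases". The primary endpoint is HPFS "as determined by blinded central review of follow-up imaging" (Primary endpoint).
- **Entry status.** It is known before assignment, because Table 1 makes it part of eligibility: "Symptoms uncontrolled by somatostatin analogues OR morphologically progressive tumor by RECIST 1.1 criteria in the liver OR baseline tumor burden" above 25% of liver volume.
- **Primary analysis.** Under Statistical analysis, a hazard rate is estimated in each arm, and the range of the log-hazards is compared with its null distribution. No adjustment for entry status is described for this test. Models adjusted for baseline variables are described for the secondary time-to-event outcomes and for continuous and binary outcomes.

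**The concern.** Blocks within institution do not control the trial-wide count of a subgroup that is not a stratum. If an imbalance in that subgroup is seen during accrual and then acted on, something outside the stated scheme has to change: the ratio, the strata, the assignments or the flow of patients. The sentence leaves open which of these it is, and when it happens.

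In an open-label trial, past assignments are known to those treating the patients. A rule that says only that adjustment will be made if needed lets later allocation depend on earlier allocation through someone's judgement. A balancing rule that uses baseline data only, is fixed in advance, runs inside the central program and keeps a random element does not carry this risk. The wording does not confine the adjustment to a rule of that kind.

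At stake is the freedom of the three-arm HPFS comparison from selection, for a factor that was available as a stratum or covariate from the start. Blinded central reading protects against biased assessment of progression. It does not protect against biased allocation.

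**Working it through.** **1. The plan's own figure.** The plan gives no number for this point. Its power statement supplies the scale. Assume exponential HPFS, 24 months of uniform accrual, 24 months of minimum follow-up, a median of 11 months on bland embolization and HR 1.78. Two arms of 60 then yield about 96 events. Pairwise power at two-sided 10% is Φ(√95.9/2 × ln 1.78 − 1.645) = Φ(2.823 − 1.645) = 88.1%, against the stated 87%. The stated power is not in dispute. The two yardsticks taken from it are the target effect, ln(1.78) = 0.577, and the standard error of a pairwise log HR, √(4/96) = 0.204.

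**2. Inputs that the article does not give.** These are assumptions:

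- share of symptomatic, non-progressive patients: one third of 180, that is 60 (range tried: 10% to 40%);
- HR for hepatic progression in this group relative to the others: 0.5 to 0.7.

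**3. Chance imbalance if allocation is left alone.** With arms fixed at 60 and m of 180 patients in the subgroup, write f = m/180. The count in one arm is hypergeometric with variance 60 × f(1 − f) × 120/179, and the covariance between two of three equal arms is minus half of that. So

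Var(difference) = 3 × 60 × f(1 − f) × 120/179.

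With f = 1/3: 180 × (1/3)(2/3) × 120/179 = 26.8. The SD is √26.8 = 5.2 patients, and 5.2/60 = 8.6 percentage points.

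**4. Effect of a one-SD imbalance on the unadjusted log HR** (approximation: difference in proportions × log prognostic HR):

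| Prognostic HR | Shift in log HR | Share of ln(1.78) | In standard errors |
|---|---|---|---|
| 0.7 | 0.0863 × ln(1/0.7) = 0.031 | 5% | 0.15 |
| 0.5 | 0.0863 × ln(1/0.5) = 0.060 | 10% | 0.29 |

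**5. Sensitivity to the share.** The same formula gives an SD of 3.3 patients at 10%, 4.4 at 20% and 5.4 at 40%. Across 10% to 40%, the shift runs from 0.020 (10%, HR 0.7) to 0.062 (40%, HR 0.5). The conclusion does not depend on the one-third figure.

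**6. How often an imbalance would invite action.** In a simulation with three independent binomial arms of 60, the largest-minus-smallest subgroup count averages 3.9 patients at a 10% share and 6.4 at 40%. The 95th percentiles are 8 and 13. Some visible imbalance is therefore to be expected, and the clause is likely to be tested in practice.

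**7. Result.** The imbalance that the clause guards against is common but has a small effect. It concerns a measured baseline factor, so stratifying or adjusting the analysis largely removes it.

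**The case against.** The strongest reply is that the sentence is being read harshly. Randomization is central, block lengths vary at random, and assignment is produced by a program. Adjustment could mean adding a stratum or a covariate-adaptive rule inside that program, which would be benign. The operational detail may also sit in a full protocol that is not shown. Most of this stands, and it rules out several stronger readings:

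- **That assignments are overridden by hand.** A reader might infer this, but the article does not say so.
- **That concealment is lost.** Open-label treatment is not the same as unconcealed allocation. Nothing shows that a site could predict its next assignment under central randomization with random block lengths.
- **That the plan regards this group as having a different outlook.** The article gives no reason for the monitoring and makes no prognostic claim.
- **That type I error is inflated by a known amount.** One can construct a case. Suppose the groups of better and worse prognosis are of equal size, with prognostic HR 0.5 to 0.7 and median about 15 months. Shifting 3 patients' worth of prognosis per arm in opposite directions gives a null HR of 1.04 to 1.07 and a pairwise error of about 0.105 to 0.12 at nominal 0.10. Six patients give 1.07 to 1.15 and about 0.12 to 0.17. No passage describes such steering. Genuine balancing on a baseline covariate tends instead to make an unadjusted test conservative.

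What does not stand is the view that this is only condensed detail. The article states an open-ended rule whose declared purpose is to influence balance between arms. That sits uneasily with its own account of automatic block assignment.

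**Conclusion.** The point holds as an avoidable risk, not as demonstrated bias. As worded, the Randomization section allows a discretionary change to allocation during open-label accrual, on a factor already known at eligibility. The primary test, as the article describes it, does not account for that factor.

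The clause has little to offer in return. Under the stated assumptions, a typical chance imbalance moves the log HR by 0.03 to 0.06. That is 5% to 10% of the effect the trial is powered for and less than a third of a standard error. If the true share or prognostic strength lies outside the assumed ranges, the size changes. The remedy does not, because it uses data that are collected before assignment in any case. Sample size, the 1:1:1 ratio and the stated power are unaffected. The change is worth making, but the point does not call the randomization as such into question.

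**What to change.** 1. In the Randomization section, delete the closing phrase that provides for adjustment, and leave the random sequence as generated. Monitoring for description only can stay.
2. Define entry status (symptomatic but not progressive versus other) from the eligibility forms. The Table 1 criteria can overlap, so state in advance where patients who enter on tumor burden alone, or who meet several criteria, are placed.
3. Account for entry status in the primary HPFS comparison. For example, estimate the arm log-hazards from a model stratified by or adjusted for entry status. The range needs only differences between arms, so one arm can serve as reference. The null distribution must then match the adjusted estimates and their covariance.
4. If balance in allocation is still wanted, apply it only as a prespecified factor inside the central program, with a random element kept, from a documented date. Crossing this factor with institution would give sparse strata, since 180/16 is about 11 patients per site. Trial status reports enrollment from March 2017, so this would be a mid-accrual change and is the less attractive option.

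Steps 1 to 3 cost a few sentences of protocol text, slightly more analysis work and a small change to how the range statistic is computed. No patients or data items are added.
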